#### Objectives 4+6: behaviour, adherence and safety concerns of people who shielded; experiences and views of healthcare providers

We will undertake thematic analysis of interviews with people who shielded and healthcare professionals.^44^ Our analysis team will include public contributors and clinical experts alongside experienced researchers. Analysis will be informed by the logic model (objective 1).^32 33^ Where appropriate, anonymous excerpts will be included in reports and peer-review papers.

#### Objective 5: costs of the shielding intervention against its consequences

We will estimate NHS healthcare resource use through anonymised linked data, compared between shielded and non-shielded matched cohorts. ED attendances, hospital admissions, length of stay, ICU admissions and GP contacts (if available) will be accessed within the SAIL Databank and costed using published unit costs.^45 46^ Cost–consequences analysis will compare costs of shielding (including implementation cost and changes in healthcare costs) with COVID-19-related outcomes such as morbidity, mortality and health-related quality of life based on SF-12 questionnaire responses^34^ from a stratified random sample of people from shielded and control cohorts. Net monetary benefit will be calculated to weigh up all costs and outcomes of the intervention.

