## Methods and analysis

See table 1 for an overview of objectives, methods and outputs.

**Table 1 T1:** Summary of methods and outputs against study objectives

Objective	Method	Output
1. Capture rationale for UK shielding.	Interviews with policy-makers.	Logic model to describe components, outcomes and mechanisms of shielding.
2. Assess effects of shielding in the general population and subgroups in terms of deaths, hospitalisations, safety and self-reported health.	Comparison of anonymised routine data between shielded population and comparator group.	Comparative outcomes for shielded and matched non-shielded people: COVID-19 tests, PCR-confirmed infections and deaths. All-cause mortality. Emergency department attendances, emergency hospital admissions, days spent in hospital, ICU admissions and days spent in ICU.
	Questionnaire to stratified random sample of intervention and control groups.	Self-reported health-related quality of life, anxiety, depression and loneliness.
3. Assess the infection and immunity within the shielded and control populations as a whole.	Analysis of routine records of blood tests in shielded population. Analysis of blood samples from stratified random subsample of intervention and control groups.	Detailed analysis of COVID-19 antigen and antibody test results within the shielded and comparator populations, to understand: Effects of shielding on infection and immunity across the population and for clinical subgroups including cancer. Impact of immunological status on outcomes in the shielded and non-shielded population.
4. Explore behaviour, adherence and safety concerns relating to shielding.	Interviews with 40 individuals and carers/household members who were shielded.	Experiences of shielded people and their carers or household members during the COVID-19 lockdown, including behaviour, emotional effects and safety concerns.
5. Assess costs of the shielding intervention against its consequences.	Investigation of costs and cost–consequences of managing and delivering shielding.	Costs of intervention implementation and subsequent healthcare resource use compared with consequences and outcomes, net monetary benefit.
6. Understand the experiences and views of healthcare providers in relation to the shielding intervention and perceived effects, including healthcare associated harms.	Interviews with 30 community-based health professionals.	Experiences of clinicians delivering care to shielded population during pandemic.

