### Intervention

Individuals on the Shielded Persons List identified as CEV were sent advice (table 2), by letter (dated 24 March 2020) email or text, to stay at home for 12 weeks and ‘do not go out at all’ plus to minimise contact with anyone in the same household or visiting to provide care, ‘even friends and family’.^27^ Correspondence after the first 12-week shielding period reflected an easing, then reinstatement, then more easing.^28–31^

**Table 2 T2:** Shielding advice given to clinically extremely vulnerable (CEV) people

Key points	Do not leave the house to go to work or to see other people
	Avoid being in the same room as another person
	Keep three steps away from another person in the home
	Avoid sharing kitchen, bathroom or bedroom facilities with others in the home
	Eat meals separately from other household members
	Be aware that hospital appointments and treatment may be postponed or cancelled
Support	Letters included details of available support, including how to obtain food, prescriptions and other information
Repeat advice	Letters were sent to CEV people throughout the pandemic which updated current advice.
	Correspondence after the first 12-week shielding period reflected an easing of some of the above points until January 2021 when shielding advice was reinstated. Advice remained, with some amendments, until August 2021. Shielding officially ended in March 2022.

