#### Objective 5: costs of the shielding intervention against its consequences

We will investigate implementation costs, including costs incurred in identifying those asked to shield and in managing shielding processes. We anticipate this will include costs of:

Developing and implementing algorithms (Public Health Wales; NHS Wales Shared Services; DHCW, formerly called National Wales Informatics Service) to identify defined categories of patients.Identifying additional patients within the NHS (via general practice registers, outpatient lists, etc).Managing and sending out shielding advice letters (NHS Wales Shared Services; NHS Wales Delivery Unit).Sharing lists and sending out support letters to shielded people from local authorities (NHS Wales Shared Services/Delivery Unit; Unitary Authorities across Wales).Sharing and sending messages to shielded people from supermarkets for prioritised delivery slots (NHS Wales Shared Services/Delivery Unit/Supermarkets).Providing food parcel deliveries/pharmacy prescription pick-ups and delivery (Unitary Authorities).

We will collect these data through interviews and documentary evidence from key informants at the organisations which collaborated in delivering this intervention. We will describe the consequences of shielding in terms of healthcare resource use based on patient-level linked data extracted from SAIL (and costed using published unit costs) and COVID-19-related morbidity and mortality and summarise net monetary benefits of shielding.

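### Objective 5 costs healthcare use of any cause but names only COVID-19-related morbidity and mortality, plus SF-12 from 12-month responders, as outcomes, so non-COVID deaths have no stated place in net monetary benefit

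*Protocol article*

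**What the plan says.** Protocol article, Analysis, Objective 5. The resource use to be costed and compared between cohorts is listed as follows: "ED attendances, hospital admissions, length of stay, ICU admissions and GP contacts (if available) will be accessed within the SAIL Databank". Nothing limits it to COVID-19 care. The cost-consequences analysis will then "compare costs of shielding (including implementation cost and changes in healthcare costs) with COVID-19-related outcomes such as morbidity, mortality", and the list continues "and health-related quality of life based on SF-12 questionnaire responses". The section closes: "Net monetary benefit will be calculated to weigh up all costs and outcomes of the intervention".

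Protocol article, Methods for each objective, Objective 5. The consequences are to be described through healthcare resource use from linked data, together with "COVID-19-related morbidity and mortality and summarise net monetary benefits of shielding". SF-12 is not mentioned there.

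Table 1 gives the Objective 5 output with no COVID-19 restriction: "Costs of intervention implementation and subsequent healthcare resource use compared with consequences and outcomes, net monetary benefit". Under Objective 2 the same table already lists "All-cause mortality. Emergency department attendances, emergency hospital admissions, days spent in hospital, ICU admissions and days spent in ICU" as comparative outcomes for the two cohorts.

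Table 2 (Intervention) records that people advised to shield were told: "Be aware that hospital appointments and treatment may be postponed or cancelled".

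**The concern.** The two sides of the economic comparison have different scopes. Costs move with any change in the listed services, whatever the cause. The only deaths named on the outcome side are COVID-19-related. If an admission for another disease does not take place, the cost side improves. If the patient then dies of that disease, no named consequence records it.

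The protocol itself expects this pathway. Table 2 warns of deferred care, the Introduction names access to medical care among the emerging effects of shielding, and Objective 6 asks about healthcare-associated harms. Net monetary benefit is the single figure in which costs and outcomes are combined, and the study is meant to inform policy in future pandemics. If the outcome set is settled only once results are known, the choice could alter the economic conclusion.

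**Working it through.** The document states no economic figure to reproduce, so the check is mainly a comparison of the text.

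**Scope as written**
- Costs (Analysis, Objective 5): implementation plus changes in healthcare costs, from any cause. The list is specific. Outpatient care is not named, and GP contacts enter only if obtainable.
- Mortality and morbidity (Methods and Analysis, Objective 5): COVID-19-related in both places. All-cause mortality appears in neither.
- Quality of life (Analysis, Objective 5): SF-12, a general health measure, although it is listed under COVID-19-related outcomes.
- Net monetary benefit (Analysis, Objective 5) and Table 1: all outcomes, with no COVID-19 limit.

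The second and fourth lines cannot both define what enters net monetary benefit.

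**What SF-12 can recover.** It is collected at 12 months, with 533 responses expected from 1333 questionnaires per cohort (533/1333 = 40%). Responders are alive at 12 months. SF-12 can therefore reflect part of the morbidity from forgone care, but none of the mortality.

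**Which way the omission acts.** Write NMB = λ × (QALYs gained) − (added cost), where λ is the value placed on a QALY. Leaving out non-COVID deaths drops the term λ × (QALYs lost per death) × (excess non-COVID deaths under shielding), which should be subtracted. If the excess is positive, the result flatters shielding. If it is negative, the result understates shielding. The document does not tell us the sign.

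**Illustration only.** Apart from the cohort of about 120 000 (Objective 2 methods), every input is assumed.
- Forgone admissions of 10 to 50 per 1000, at GBP 1,500 to 4,000 each:
  - low: 120 000 × 10/1000 × 1,500 = GBP 1.8 million
  - high: 120 000 × 50/1000 × 4,000 = GBP 24.0 million
- Excess non-COVID deaths of 0.2 to 2 per 1000, 2 to 5 QALYs lost each, λ = GBP 20,000:
  - low: 120 000 × 0.2/1000 × 2 × 20,000 = GBP 0.96 million
  - high: 120 000 × 2/1000 × 5 × 20,000 = GBP 24.0 million
- Saving minus loss:
  - smallest: 1.8 − 24.0 = GBP -22.2 million
  - largest: 24.0 − 0.96 = GBP +23.0 million

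On these inputs the saving alone is always positive, while the net of the two terms can take either sign. This shows that the scope of the outcome set can matter. It does not estimate the effect.

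**The case against.** A reader might infer that the plan credits every change in NHS use, weighs it against COVID-19 outcomes alone, leaves the harm of forgone care out entirely, and so biases net monetary benefit in favour of shielding. The documents do not support that, for these reasons:

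- SF-12 stands in the same list and is a general measure, so some non-COVID morbidity is captured.
- The Objective 5 methods section already treats resource use as a consequence as well as a cost.
- The costed list does not name outpatient care, and the admissions listed in Table 1 are emergency ones. Some deferred planned care may therefore never appear as a saving.
- Deferred care could return as emergency attendances or admissions, which would raise costs.
- The list of COVID-19-related outcomes is given as examples, and the closing sentence of the section is broad. The text is inconsistent on scope rather than explicit in excluding non-COVID deaths.
- All-cause mortality is compared under Objective 2, and safety concerns are explored under Objectives 4 and 6, so the study as a whole does not hide the harm.

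Two further arguments are fair but do not settle the matter. The protocol concedes that the comparator is imperfect, so all-cause mortality would carry residual case-mix differences into net monetary benefit. That is a reason to show both versions, not to omit one. An article also leaves to a fuller plan how deaths and utilities are valued. However, the COVID-19 restriction is stated here, twice, and it conflicts with the stated scope of the result.

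**Conclusion.** The point holds as an internal inconsistency with a practical consequence. Objective 5 costs the listed healthcare use whatever its cause, attaches a COVID-19 limit to morbidity and mortality in both of its sections, and then promises a net monetary benefit covering every cost and outcome. Non-COVID deaths have no named place, and SF-12 fills the gap only in part.

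Neither the direction nor the size of any bias is shown. The direction depends on whether shielding raised or lowered non-COVID deaths. The size would need unit costs, numbers of forgone admissions, QALYs lost per death and a QALY value, none of which the document gives. The change of sign in the illustration rests on assumed inputs. This is a scope to reconcile before analysis, not a demonstrated bias.

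**What to change.** In both Objective 5 sections (Methods and Analysis), name all-cause mortality as a consequence entering net monetary benefit, alongside COVID-19 mortality. Because all-cause deaths include COVID-19 deaths, give net monetary benefit in two versions, one on each basis, rather than adding the two counts together. Report COVID-19 and non-COVID-19 outcomes and resource use separately, so that a fall in non-COVID care can be read next to non-COVID deaths.

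The cost is a few sentences in the protocol and the economic analysis plan, plus one further set of results. Mortality needs no new data collection, since Objective 2 already compares all-cause mortality between the cohorts. The downside is that all-cause effects are noisier and more exposed to residual case-mix differences between the cohorts, which is why both versions should be shown.

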### Study design limitations

As the shielding intervention was introduced across all the UK at one timepoint, we are able to carry out a quasiexperimental study only, with no clear historic or concurrent control group. In this circumstance, we acknowledge that any method to identify a matched comparator group is, to some extent, flawed. As entire clinical codes were allocated to the CEV (shielded) group, we intend to match as well as we can, from routine data sources, by age, sex and health service utilisation in the year prior to introduction of the shielding policy. We will then compare clinical, demographic and socioeconomic characteristics of our two groups and adjust for differences in our analysis. Without any group for comparison of outcomes it is difficult to draw any conclusions related to the benefits, harms and costs of the shielding policy. We have, therefore, selected this study design as the best available for this study.

The study was designed before widespread availability of vaccinations. We do not intend to include this variable in our data collection and analyses; so many variations in timing, vaccination delivered, number of vaccinations and boosters means this analysis is outside the scope of the current study.

Although not all those included in the shielding intervention will have received letters or complied with advice, and some people in the non-shielding cohort may have strictly self-isolated, we are following principles of analysis by intention to treat or treatment allocated^47^ as this is most suited to a pragmatic evaluation context where study findings relate to how the intervention was implemented, not just how it was intended.

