**Methods and analysis:**

This is a quasiexperimental study undertaken in Wales where records for people who were identified for shielding were already anonymously linked into integrated data systems for public health decision-making. We will: interview policy-makers to understand rationale for shielding advice to inform analysis and interpretation of results; use anonymised individual-level data to select people identified for shielding advice in March 2020 and a matched cohort, from routine electronic health data sources, to compare outcomes; survey a stratified random sample of each group about activities and quality of life at 12 months; use routine and newly collected blood data to assess immunity; interview people who were identified for shielding and their carers and NHS staff who delivered healthcare during shielding, to explore compliance and experiences; collect healthcare resource use data to calculate implementation costs and cost–consequences. Our team includes people who were shielding, who used their experience to help design and deliver this study.

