### Participant identification and participation (objectives 2–5)

Eligible participants will include those identified as CEV in Wales between March and May 2020 and who were advised to shield (shielded cohort). We will use individual-level population-scale anonymised data within the Secure Anonymised Information Linkage (SAIL) Databank to identify those shielded and their linked Electronic Health Records (EHR) from routinely collected NHS data sources, Office for National Statistics data and other health and administrative data, including the Wales Multimorbidity Cohort COVID-19 extension, under existing Information Governance Review Panel (IGRP) approvals.^26^ We will also identify a cohort to match those identified for shielding with partners in Digital Health and Care Wales (DHCW), through cohort ‘propensity’ matching variables including age, sex and historic health service utilisation. We will create a stratified random sample from each of the two cohorts for questionnaire distribution and blood sample collection. Prospectively collected data from questionnaires and bloods will be linked back into the SAIL Databank for anonymised linkage. Figure 1 describes data flow. Figure 2 describes recruitment and participation.

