We will use anonymised individual-level linked routinely collected anonymised EHR data to compare outcomes between the two cohorts—COVID-19 infections, deaths, hospitalisations, immunity status, safety and costs up to 12 months. Inclusion of approximately 120 000 people in each cohort—from date of their addition to the shielding list between 23 March and 31 December 2020; and from 23 March 2020 for the matched control groups: with follow-up of outcomes up to 1 year—gives ample power to detect small differences (standardised statistical effects as small as 0.05, 90% power, 5% significance) in outcomes between groups and between most subgroups. For instance, 3%–5% of each cohort will be recorded as belonging to a black, Asian or other minority ethnic group, allowing comparison of outcomes between up to 6000 people per subcohort; larger numbers will be included in clinical subgroups such as cancer, heart disease, diabetes. We recognise it will not be possible to completely mirror the shielded group in our matched cohort. Our statistical analysis plan will incorporate ways of characterising differences and making appropriate adjustments.We will examine self-reported outcomes at 12 months. We will distribute 1333 postal questionnaires (with online response option) (online supplemental appendix 1) to a stratified random sample in each of the shielded and non-shielded (matched) cohorts to achieve 533 responses in each. Questionnaires will include: the health-related quality-of-life measure (SF12);^34^ measures of common mental disorders, anxiety and depression (PHQ9, GAD7);^35 36^ safety concerns and behaviour during COVID-19 lockdown (staying home, isolating—including within home). Our sample size is sufficient to detect an average difference of 2.5 in SF12 component scores (standardised statistical effect 0.2, 90% power, 5% significance). Our Wales NHS partners, who hold contact details of individuals, will send the questionnaires and assign each an anonymised ID number. This will ensure that the research team has no identifying information about participants at any stage of the evaluation.

10.1136/bmjopen-2021-059813.supp1Supplementary data

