#### Objective 2: effectiveness of shielding

We will analyse quantitative data following ‘intention to treat’ analysis principles. Our detailed statistical analysis plan, compliant with Swansea Trials Unit’s Standard Operating Procedure,^42^ will cover: descriptive summaries of study data and thematic categorisation; formal comparison of outcomes, adjusted for case mix and potential confounding factors; statistical modelling strategy underpinning comparisons, including conventions for dealing with missing data, selection of confounders; reporting of analyses. Modelling will use generalised linear and survival multilevel models for events, counts and time to events. Entry dates are based on the date identified as CEV (shielded cohort) or 20 March 2020 (matched cohort); 12-month follow-up data will be censored by death, or known date of migration from Wales.

There was considerable spatial as well as temporal variation in the (estimated) R number across Wales during our study window, with little detailed data on the accuracy of these estimates. Although difficult to justify incorporation of such estimates into formal models, we will use what is known to inform discussion of our results. We will assess if available anonymised residential identifiers allow creation of usable household/residential clusters, and, if so, whether extension to include clustering improves our models. We will consider further use of care home residence identifiers and critical care and hospital in-patient spells in defining potential explanatory covariates and factors for inclusion in models.

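### The matching history stops when the policy began, but shielded entry may run to December 2020, so anyone listed later after new illness would be matched on an out-of-date history

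*Protocol article*

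**What the plan says.** **Matching.** Under Study design limitations, the groups are matched "by age, sex and health service utilisation in the year prior to introduction of the shielding policy". The section on participant identification is looser: matching works "through cohort ‘propensity’ matching variables including age, sex and historic health service utilisation", with no dates and an open list of variables.

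**Entry.** The methods section for Objective 2 counts shielded people "from date of their addition to the shielding list between 23 March and 31 December 2020". The analysis section for the same objective agrees that entry is personal: "Entry dates are based on the date identified as CEV (shielded cohort) or 20 March 2020 (matched cohort"). The methods section gives the controls a slightly different fixed date: "and from 23 March 2020 for the matched control groups".

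**Who is in the shielded cohort.** Two other statements are narrower. Participant identification says "Eligible participants will include those identified as CEV in Wales between March and May 2020". The abstract says the study will "select people identified for shielding advice in March 2020 and a matched cohort".

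**What the matching is for.** The methods section for Objective 2 relies on prior service use to bring the comparator close to the shielded group, and then plans a difference-in-difference comparison of service use before and after the policy. Study design limitations adds that clinical, demographic and socioeconomic characteristics will be compared after matching and adjusted for.

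**The concern.** The look-back is fixed in calendar time, while entry to the shielded cohort is personal. For someone listed in March 2020 the two coincide. For someone listed months later, the history used to choose a control ends well before that person's follow-up starts.

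The Introduction names cancer, transplants and immunosuppressant treatment among the reasons for listing, and any of these can begin during 2020. A person whose illness started after March 2020 would look like a lower user of services in the matching year and would be paired with a lower-risk control. The illness then shows up in follow-up as extra deaths, admissions and cost on the shielded side. Shielding would tend to look more harmful or more costly, or a real benefit would be hidden.

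The difference-in-difference step does not clearly remove this. It cancels differences that stay constant, whereas illness that begins between baseline and follow-up gives a quiet before-period and a heavy after-period. It also applies to service use, not to mortality, which has no before-period.

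**Working it through.** **Inputs, all from the protocol article**
- End of the matching year: start of the policy, taken as 23 March 2020 (methods, Objective 2). Alternatives are 20 March (analysis, Objective 2) and 24 March (letter date, Intervention section).
- Last shielded entry: 31 December 2020 (methods, Objective 2), 31 May 2020 (participant identification) or 31 March 2020 (abstract). The month-ends are my reading of the months named.
- Cohort size: about 120 000 each. Power statement: standardised effect 0.05, 90% power, 5% significance, taken as two-sided.

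**Step 1. The plan's own figure.** No stated figure bears on the look-back. The nearest is the power statement. Required size per cohort = 2 × ((1.95996 + 1.28155) / 0.05)² = 8406, so 120 000 is indeed ample.

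**Step 2. Longest gap between the end of the look-back and entry, in days**

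| Look-back ends | Last entry 31 March | Last entry 31 May | Last entry 31 December |
|---|---|---|---|
| 20 March | 11 | 72 | 286 |
| 23 March | 8 | 69 | 283 |
| 24 March | 7 | 68 | 282 |

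**Step 3. The gap as a share of a year.** 283 / 365.25 = 0.775 and 69 / 365.25 = 0.189. For a 31 December entrant, about 23% (1 − 0.775) of the 12 months before entry lies in the matching window. For a 31 May entrant it is about 81% (1 − 0.189).

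**Step 4. Form of the bias.** Let *p* be the share of the shielded cohort listed because of illness that began after the look-back ended. Let *d* be the excess outcome risk of these people over the controls chosen on their earlier history. With no effect of shielding and no further adjustment, the cohorts differ by *p* × *d*. The article gives neither *p* nor *d*, so no number follows.

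**Step 5. Would a small bias be lost in sampling error?** The standardised difference detectable with 90% power at 120 000 per cohort is (1.95996 + 1.28155) × √(2 / 120 000) = 0.013. A bias of that order would therefore usually reach nominal significance, so the large sample gives no protection.

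**The case against.** The strongest reply is that the affected group may be small or absent.

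- **Entry window.** Only the methods section for Objective 2 gives 31 December. The eligibility text says March to May 2020, under which nobody listed in the autumn would be included. A reader might infer that entry to December is settled. It is one side of an unresolved contradiction. This stands, and it makes the point conditional.
- **Reason for late listing.** A reader might infer that late listing means new illness. The Introduction gives only one reason for the list growing, the refinement of criteria in May 2020. The methods mention people missed by the initial choice of conditions or by administrative error, and the costing section mentions extra patients found from practice registers and outpatient lists. Such people could have had their condition, and its service use, inside the matching year. The Introduction also puts the Welsh list at 133 000 by July 2020, already above the planned 120 000, and nothing shown points to a large autumn intake. This stands too.
- **Adjustment.** Differences in characteristics will be examined and adjusted for. That could reduce the problem if covariates are measured at each person's entry. The article does not date them, and that detail may sit in the analysis plan. The article also says that whole clinical codes went to the shielded group, so few controls may share the condition that needs adjustment.
- **Merit of a fixed window.** It keeps lockdown months out of the baseline. Personal look-backs would bring them in, and matching on the work-up just before listing carries some risk of regression to the mean. This is a fair trade-off, and the fix has to allow for it.

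None of this removes the mismatch between the stated look-back and the stated entry rule.

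**Conclusion.** The point holds, conditionally. As written, the look-back ends at policy start while shielded entry is personal. If entry runs to 31 December 2020, the matching history can be up to 283 days old at entry. If it closes at the end of May, the maximum is about 69 days. If it is confined to March, the gap is about a week and the point largely falls away.

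Bias follows only for people listed because of illness that began after March 2020, and its likely direction is against shielding. Its size cannot be computed, because neither the number of such people nor their excess risk is given.

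Two stronger readings are tempting. One is that the match tells us nothing about later entrants and that new illness falls only in the shielded cohort. The documents do not support this: part of the history may still be relevant, and the article does not say how controls who later become vulnerable are handled. The other is a definite number of excess deaths or percentage points. Any such figure would rest on late-entry shares and mortality rates that the article does not contain.

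**What to change.** 1. State one entry window for the shielded cohort and use it in the abstract, the participant identification section and the methods for Objective 2.
2. If later entrants stay in, match by calendar month of listing. Give each control the index date of the matched shielded person. Measure service use and the adjustment covariates for both over the same 12 calendar months before that date, so that pandemic falls in service use affect both alike.
3. Keep the fixed pre-policy year as the difference-in-difference baseline or as a sensitivity analysis.
4. Report covariate balance and results separately for people listed at the start and people listed later, with the number in each group.

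**Cost.** The work is a change of wording and a rerun of the matching by month in routine linked data, with no new data collection. The drawbacks are more programming, possibly fewer matches among late entrants, pandemic months in their look-back, and some risk of regression to the mean from work-up before listing. Steps 3 and 4 let a reader see whether these matter. Re-anchoring will not supply controls with the same qualifying diagnoses; that limitation remains.
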